#### Predictor variables and covariates

Primary prognostic predictor variables have been selected based on established clinical and biological plausibility for predicting consciousness recovery: (1) etiology of brain injury (TBI, hypoxic-ischaemic encephalopathy, cerebrovascular event, metabolic/toxic encephalopathy, other), given that neurobiological recovery trajectories differ substantially across aetiological subgroups; (2) injury severity at the acute phase (GCS score at hospital admission); (3) time from acute brain injury to study enrollment; (4) CRS-R subscale scores at baseline (auditory, visual, motor, oromotor/verbal, communication, and arousal subscales); and (5) neuroimaging characteristics (white matter integrity on DTI, functional connectivity on fMRI). Pre-injury lifestyle characteristics [smoking status, alcohol consumption, physical activity (assessed via caregiver proxy report using IPAQ) (11), and dietary habits] are retained as exploratory secondary covariates; their collection is hypothesis-generating and their role as determinants of post-injury recovery will be interpreted with appropriate caution given the reliance on caregiver proxy report.

Pre-specified adjustment covariates in all multivariable models include age, sex, educational level, and comorbidities (e.g., cardiovascular disease, diabetes mellitus, chronic kidney disease). It should be noted that injury severity (GCS at acute admission) and the interval from injury to enrollment are designated as primary prognostic predictor variables in this study (see above), rather than as confounders, given their established direct effects on consciousness recovery trajectories; they will therefore enter the analytical models as predictors of interest rather than as adjustment terms. Effect modifiers—including age stratum (< 50 years vs. ≥50 years), injury type (traumatic vs. non-traumatic), and baseline CRS-R score—will be formally evaluated through prespecified subgroup analyses and interaction testing.

### Data sources and measurements

All baseline data will be collected within 2 weeks of enrollment at the Department of Rehabilitation Medicine, Guangdong Sanjiu Brain Hospital, to ensure data consistency and minimize recall bias.

Demographic, lifestyle, medical history, and family history data will be collected via structured questionnaires administered by trained research personnel during face-to-face interviews. Questionnaire items include: age (years), sex (male/female), educational attainment (primary/secondary/tertiary), occupation (employed/retired/unemployed), marital status (single/married/divorced/widowed), smoking status (never/former/current), alcohol consumption (frequency and quantity), physical activity level [assessed by IPAQ (11)], dietary habits (frequency of fruit, vegetable, and processed food intake), detailed prior diagnoses (TBI, stroke, hypoxic–ischemic encephalopathy, etc.), current medication use (drug name, dose, and duration), and relevant disease history in first-degree relatives.

Physical examinations will be performed under standardized conditions by a consistent team of trained physicians to minimize measurement variability. Anthropometric measurements include height (measured to ±0.1 cm using a stadiometer), body weight (measured to ±0.1 kg using a calibrated electronic scale), body mass index (BMI, calculated as weight [kg]/height [m]^2^), and waist and hip circumferences (measured with a flexible tape). Blood pressure will be measured using an automated sphygmomanometer after at least 5 min of rest, with the mean of two to three readings recorded at 1-min intervals. Additional vital signs include heart rate (beats per minute) and body temperature (°C).

Laboratory analyses will be performed on blood and urine samples collected following overnight fasting, processed according to standardized protocols at the accredited clinical laboratory of Guangdong Sanjiu Brain Hospital. Blood tests include: complete blood count (CBC); lipid profile (total cholesterol, low-density lipoprotein cholesterol [LDL-C], high-density lipoprotein cholesterol [HDL-C], and triglycerides); fasting plasma glucose; glycated hemoglobin (HbA1c); renal function (estimated glomerular filtration rate [eGFR], calculated using the CKD-EPI equation); and disease-specific biomarkers, including inflammatory markers (C-reactive protein [CRP] and interleukin-6 [IL-6]) and neurotrophic factors (brain-derived neurotrophic factor [BDNF]). Urinalysis includes routine urinalysis and urine albumin-to-creatinine ratio (ACR) to evaluate renal function and detect early signs of complications.

### Neuroimaging and neurophysiological assessment protocols

Structural MRI (3 T): T1-weighted (MPRAGE, 1 mm isotropic), T2-weighted FLAIR, and susceptibility-weighted imaging (SWI) will be acquired using a standardized protocol on a 3 T Siemens Prisma scanner. Lesion localization and volumetrics will be quantified using FreeSurfer v7.4 (cortical thickness, subcortical volumes) and SPM12 (lesion overlay analysis).

Diffusion Tensor Imaging (DTI): 64-direction DTI will be acquired (b = 1,000 s/mm^2^) and preprocessed using FSL v6.0 (eddy current correction, motion correction, tensor fitting). Primary indices: fractional anisotropy (FA) and mean diffusivity (MD) in the corticospinal tract, thalamocortical projections, and corpus callosum, derived using tractography with the MNI white matter atlas as reference.

Resting-State fMRI (rs-fMRI): A 10-min eyes-closed resting-state acquisition (TR = 2 s, TE = 30 ms, 3 mm isotropic) will be preprocessed using fMRIPrep v23.2 (motion scrubbing: FD > 0.5 mm, DVARS > 1.5; band-pass filtering: 0.01–0.1 Hz; spatial smoothing: 6 mm FWHM). Primary derived indices: (1) default mode network (DMN) internal functional connectivity (seed-based analysis using posterior cingulate cortex as reference seed); (2) thalamocortical connectivity (bilateral thalamic seeds); and (3) amplitude of low-frequency fluctuations (ALFF).

EEG: 64-channel EEG will be acquired during a 30-min resting-state paradigm and preprocessed using EEGLAB v2023.0 (independent component analysis for artifact rejection; re-referencing to average; band-pass filtering: 0.5–40 Hz). Primary derived indices: (1) spectral power in delta (0.5–4 Hz), theta (4–8 Hz), alpha (8–13 Hz), and beta (13–30 Hz) bands; (2) microstate analysis (4-class canonical microstates, mean duration, frequency, and global explained variance); and (3) perturbational complexity index (PCI).

Covert Consciousness Detection Protocol: Motor imagery (MI) paradigms will be administered to all participants with sufficient behavioral arousal (CRS-R arousal subscore ≥1). The standardized paradigm requires participants to imagine squeezing their right hand (“yes”) or wiggling their toes (“no”/rest) in response to binary yes/no questions. EEG data will be analyzed using a support vector machine (SVM) classifier with 10-fold cross-validation (accuracy threshold: ≥ 70% for positive classification). fMRI motor imagery (supplementary motor area [SMA] activation) will serve as concurrent validation. All paradigms will be administered and scored by two independently trained operators blind to each other’s results; inter-rater reliability will be quantified using Cohen’s kappa.

### Follow-up procedures

Follow-up assessments will employ a hybrid surveillance strategy combining in-person evaluations with remote monitoring. Core neurobehavioral and functional assessments (CRS-R, GOS-E, DRS, EQ-5D, SF-36, FIM, HADS, and Zarit Caregiver Burden Interview) will be conducted at bedside by certified assessors at baseline and at 3, 6, 12, 24, 36, 48, and 60 months (8 assessment timepoints in total, comprising 7 in-person follow-up visits). The Chinese validated CRS-R (7) will be used throughout. Assessors must complete standardized training—covering scoring, ≥10 supervised assessments, and ICC ≥ 0.85 reliability—before independent use. The same assessor will evaluate each participant at all timepoints when feasible; if replaced, inter-rater reliability will be verified against the prior assessor’s last two evaluations. Total and subscale scores will be recorded at each visit. eMCS is defined by subscale-specific behavioral thresholds (per Primary Outcome Variables), not a total score of 23/23, which reflects full neurological recovery rather than functional communication or object use. Neuroimaging investigations (MRI/DTI/fMRI) and serum biomarkers (NfL, S100B, GFAP, and other injury-related biomarkers) will be performed at baseline and at 6, 12, 24, 36, 48 and 60 months. Following the 6-month visit, remote follow-ups will be conducted by telephone interview supplemented by caregiver-reported outcomes at 3-month intervals between scheduled in-person visits, primarily capturing vital status, rehospitalization events, and major adverse events. Remote follow-ups will be administered by uniformly trained research coordinators using standardized scripts, with video calls employed as an adjunct to confirm the patient’s general condition. In-person outpatient visits will be conducted by neurologists and rehabilitation therapists.

Follow-up assessments will capture: changes in consciousness level (CRS-R); vital status; major cardiovascular events; functional independence (Functional Independence Measure [FIM]); health-related quality of life (SF-36); caregiver burden (Zarit Caregiver Burden Interview); changes in medication or treatment regimens; activities of daily living (ADLs) and instrumental activities of daily living (IADLs); mental health status (Hospital Anxiety and Depression Scale [HADS]); and adverse event documentation. All follow-up data will be entered in real time into an electronic data capture (EDC) system, with monthly data quality reviews conducted to achieve a target follow-up completion rate of ≥ 85%.

Outcome event ascertainment procedures are as follows: recovery status will be confirmed through a composite of clinical assessments, medical record review, and neuroimaging evidence (e.g., fMRI or EEG demonstrating improved cortical activity); death events will be ascertained via civil death registration systems, family-reported notification, and hospital records, with cause-specific mortality classified as neurological deterioration, cardiovascular events, infection, or other causes; cardiovascular events will be adjudicated according to internationally accepted definitions supported by neuroimaging and laboratory evidence. Telephone interviews have been established as a feasible follow-up modality, demonstrating agreement with self-reported outcome measures in the majority of settings, achieving a cohort retention rate of 93% within 6 months in culturally adapted intervention research, and proving applicable to the longitudinal assessment of functional and cognitive recovery trajectories following neurological infections (12) (Table 1).

**Table 1 tab1:** Evaluation parameters at baseline and follow-up visits.

Evaluation parameter	Baseline (enrollment)	Follow-up (telephone/video or on-site visits)						
	(Hospital admission)	Visit 1 (3 m)	Visit 2 (6 m)	Visit 3 (12 m)	Visit 4 (24 m)	Visit 5 (36 m)	Visit 6 (48 m)	Visit 7 (60 m)
Informed consent	x							
Inclusion criteria met	x							
Demographics & medical history	x							
Vital signs & neurological exam	x							
Consciousness level (CRS-R)	x	x	x	x	x	x	x	x
Functional status (GOS-E, DRS)	x	x	x	x	x	x	x	x
Quality of life (EQ-5D)	x	x	x	x	x	x	x	x
Survival status	x	x	x	x	x	x	x	x
Rehospitalization & complications	x	x	x	x	x	x	x	x
Adverse events	x	x	x	x	x	x	x	x
Treatment records (SOC, medications, neuromodulation, including weekly contact time per discipline)	x	x	x	x	x	x	x	x
Neuroimaging (MRI/DTI/fMRI)	x			x	x	x	x	x
Biomarkers (NfL, S100B, GFAP)	x			x	x	x	x	x
Laboratory tests (CBC, electrolytes, etc.)	x							
Primary outcomes (consciousness recovery, all-cause death, major CV events)		x	x	x	x	x	x	x

× Represents data collection timepoint. CRS-R, Coma Recovery Scale-Revised; GOS-E, Extended Glasgow Outcome Scale; DRS, Disability Rating Scale; EQ-5D, EuroQol 5-Dimensions; SOC, Standard of Care; NfL, Neurofilament Light Chain; GFAP, Glial Fibrillary Acidic Protein; CBC, Complete Blood Count.

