### Study population

The target population comprises individuals currently diagnosed with pDoC—specifically VS or MCS (encompassing both MCS − and MCS+)—at the time of enrollment. Patients who have already achieved eMCS prior to enrollment are not eligible, as eMCS constitutes the primary consciousness recovery endpoint of this study. Patients with post-traumatic confusional state (PTCS), which represents a transitional state beyond eMCS in the TBI recovery trajectory, are likewise not eligible for enrollment. Both conditions are characterized by persistent alterations in consciousness following severe acquired brain injury: VS is defined by wakefulness without awareness, whereas MCS indicates the preservation of partial conscious awareness.

Inclusion criteria are as follows: (1) a confirmed diagnosis of DoC with a duration of at least 28 days, established according to the 2020 European Academy of Neurology (EAN) guidelines (6) and assessed using the validated Chinese version of the CRS-R (7), including vegetative state (VS) and minimally conscious state (MCS; encompassing both MCS − and MCS+); (2) age between 18 and 80 years; (3) provision of written informed consent by the participant (if possessing decision-making capacity) or by a legally authorized representative (LAR); and (4) availability of complete medical records documenting the etiology of the initial brain injury, injury severity, and relevant diagnostic investigations. Eligible etiologies include all forms of acquired brain injury that can lead to prolonged disorders of consciousness (pDoC), such as traumatic brain injury (including both closed and penetrating head injuries) and non-traumatic brain injury—including hypoxic-anoxic injury (e.g., due to cardiac arrest, respiratory failure, or near-drowning), cerebrovascular events (such as ischemic stroke, hemorrhagic stroke, and subarachnoid hemorrhage), and metabolic or toxic encephalopathies.

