### Variables

#### Primary and secondary outcome variables

The primary outcome variables of this study are as follows: (1) pDoC recovery, defined as emergence from MCS (eMCS), operationalized as achieving a CRS-R communication subscale score ≥2 (functional interactive communication) or a motor subscale score ≥6 (functional object use), confirmed on ≥2 standardized CRS-R assessments conducted ≥7 days apart and sustained for ≥4 consecutive weeks. This criterion applies uniformly to patients with a baseline diagnosis of VS or MCS. All recovery determinations will be adjudicated by the independent Endpoint Adjudication Committee; (2) all-cause mortality, defined as death from any cause at any point during the 5-year follow-up period (up to and including month 60). In the competing-risk analytical framework, all-cause mortality serves as the primary competing risk event for the consciousness recovery outcome. Patients who survive to the end of the 60-month follow-up without having achieved the consciousness recovery endpoint will be administratively right-censored at month 60; and (3) major cardiovascular events (MACE), encompassing myocardial infarction (defined in accordance with the Fourth Universal Definition of Myocardial Infarction, requiring elevated cardiac biomarkers in conjunction with clinical evidence of myocardial ischemia), hospitalization for heart failure (defined as inpatient admission requiring intravenous diuretics or inotropic support), and stroke (confirmed by neuroimaging [CT/MRI] with neurological deficits persisting for more than 24 h).

Secondary outcome variables include: (1) changes in functional status, assessed using the Glasgow Outcome Scale–Extended (GOS-E) and the Disability Rating Scale (DRS) (8, 9); (2) dynamic changes in biomarkers, including serum neurofilament light chain (NfL), glial fibrillary acidic protein (GFAP), S100 calcium-binding protein B (S100B), and other injury- and recovery-related biomarkers; (3) health-related quality of life, evaluated using the EQ-5D questionnaire, with caregiver proxy responses employed when direct patient assessment is not feasible; and (4) rehospitalization rate, documented by recording the frequency and causes of readmission, with particular attention to common complications such as infections, seizures, and respiratory events.

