#### Exposure variable

The primary exposure variable is the baseline level of consciousness (VS or MCS) at enrollment. All enrolled participants will receive standardized multimodal rehabilitation care in accordance with the Chinese Expert Consensus on the Diagnosis and Treatment of Prolonged Disorders of Consciousness (Standard of Care, SOC) (10), encompassing: (1) pharmacological arousal-promoting therapy (e.g., amantadine, donepezil, zolpidem); (2) multimodal sensory stimulation therapy (auditory, tactile, visual, and olfactory modalities); (3) physical therapy (including tilt-table training and passive mobilization); (4) occupational therapy; (5) speech-language therapy; (6) hyperbaric oxygen therapy (where indicated and available); and (7) neuromodulation techniques (e.g., median nerve electrical stimulation, repetitive transcranial magnetic stimulation, spinal cord stimulation), as well as evidence-based complication management (infections, spasticity, pressure injury). Treatment intensity for each modality will be quantified as total weekly contact time (minutes per week) and session frequency, recorded prospectively in the electronic data capture system at each assessment timepoint. All treatment variables will be incorporated as time-dependent covariates (operationalized as weekly contact time (min/week) per rehabilitation modality) in the analytical models to distinguish the natural disease course from treatment-mediated effects.

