### Bias control

To minimize selection bias, a systematic three-step recruitment procedure (screening, informed consent, and baseline assessment) will be implemented with independent review by a multidisciplinary team. To address follow-up bias, a hybrid surveillance strategy combining telephone interviews and outpatient visits will be employed, with a target follow-up completion rate of ≥ 85% and active tracing of participants lost to follow-up. Confounding bias will be controlled through multivariable regression models incorporating documented potential confounders, with effect modification explored in prespecified subgroup analyses. To mitigate performance and detection bias, outcome assessors will be blinded to baseline results; all primary outcome events will be adjudicated by an independent Endpoint Adjudication Committee in a blinded manner; and all neuroimaging data will be independently reviewed by two radiologists. The study has been prospectively registered on an international clinical trial registry and will be reported in accordance with the STROBE statement.

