This study achieves several important methodological advances. The rigorous prospective longitudinal design, with a 5-year follow-up period substantially exceeding that of most published studies (typically 1–2 years), enables comprehensive characterization of both the critical time windows for consciousness recovery and the features of long-term stable plateaus—directly addressing the predominant reliance on cross-sectional observations in the field and providing unprecedented longitudinal data to elucidate the time-dependent nature of recovery. In terms of data integration, this protocol transcends the limitations of traditional single-source clinical data by harmonizing structured electronic medical records, standardized neuropsychological assessments (CRS-R), objective neuroimaging (structural and functional MRI), serum biomarkers of neural injury, and patient-reported outcomes (health-related quality of life instruments). Notably, the application of internationally standardized instruments with blinded assessment for the definition of core outcome variables substantially reduces misclassification and information bias. This multisource data integration is anticipated to reveal deep associations between clinical phenotypes and biological mechanisms, uncovering interaction patterns that conventional single-modality research cannot identify. To mitigate the most critical methodological threats in DoC research—attrition bias and measurement bias—we have implemented distinctive safeguards: a hybrid follow-up strategy combining telephone interviews and outpatient visits, with a quality target of ≥ 85% follow-up completion rate; uniform training and certification of all assessors; blinded adjudication of all primary outcome events by an independent Endpoint Adjudication Committee; and independent dual-reader review of all neuroimaging data. As a single-center study, we are able to achieve a highly standardized operational workflow and quality control system, with all data collection adhering to unified standard operating procedures (SOPs). The study has been prospectively registered on an international clinical trial registry and will be reported in compliance with the STROBE statement; the level of quality control substantially exceeds the average for comparable observational studies.

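### The same-assessor rule conflicts with the claim that outcome assessors are blinded to baseline results, so by default the bedside rater of recovery also rated the exposure

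*Protocol article*

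**What the plan says.** **Who rates, and when.** Follow-up procedures states that the core assessments, CRS-R included, "will be conducted at bedside by certified assessors at baseline and at 3, 6, 12, 24, 36, 48, and 60 months". It then sets the assignment rule: "The same assessor will evaluate each participant at all timepoints when feasible". If the assessor changes, "inter-rater reliability will be verified against the prior" assessor's last two evaluations.

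**What is claimed about blinding.** Bias control says "outcome assessors will be blinded to baseline results". The Discussion counts as a strength "the application of internationally standardized instruments with blinded assessment for the definition of core outcome variables", and says that this substantially reduces misclassification.

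**What the ratings feed.** Exposure variable: "The primary exposure variable is the baseline level of consciousness (VS or MCS) at enrollment". Under Study population, that diagnosis is "assessed using the validated Chinese version of the CRS-R". Under Primary and secondary outcome variables, recovery means "achieving a CRS-R communication subscale score ≥2 (functional interactive communication) or a motor subscale score ≥6 (functional object use"), with confirmation on repeated assessments.

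**Safeguards.** Recovery needs at least two CRS-R assessments at least 7 days apart, sustained for at least 4 weeks. An independent Endpoint Adjudication Committee rules on it, blinded according to Bias control. Follow-up procedures also has recovery confirmed by a composite of clinical assessment, record review and neuroimaging evidence.

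**The concern.** The primary research question is whether baseline level (VS vs MCS) independently predicts recovery. One instrument supplies both sides of that comparison, and the default rule has one person apply it on both sides. A rater who classified the patient at baseline knows the exposure when deciding, months or years later, whether the recovery threshold is met. If that knowledge influences the score, the error depends on exposure group. It is then a differential error in the main association and not only added noise.

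The claim itself is also at stake. Readers of the eventual report will be told that core outcomes were assessed blind. Under the default procedure that would not be true of the bedside CRS-R.

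The handover rule has a separate weakness. It compares a new assessor's scores with scores from earlier visits, so a real change in the patient cannot be told apart from disagreement between raters.

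**Working it through.** **1. Can both statements be met?**

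| Step | Source in the protocol article | Consequence |
|---|---|---|
| Baseline is one of the 8 assessment timepoints | Follow-up procedures | The same-assessor rule covers baseline |
| Same assessor at all timepoints when feasible | Follow-up procedures | By default, the follow-up rater did the baseline CRS-R |
| VS or MCS is assessed with the CRS-R | Study population; Exposure variable | That rater knows the exposure |
| Recovery is a CRS-R subscale threshold | Primary and secondary outcome variables | That rater also scores the outcome |
| Outcome assessors are blinded to baseline results | Bias control | Incompatible with the rows above |

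No separate blinded CRS-R rater is described. Recruitment procedures has neurologists, rehabilitation therapists and research nurses do the baseline. Follow-up procedures has neurologists and rehabilitation therapists do the in-person visits. The two statements agree only where the same-assessor rule turns out not to be feasible.

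**2. How old are the last two evaluations at a handover?** Using the scheduled in-person visits:

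| Handover at month | Last two scheduled evaluations (month) | Age in months |
|---|---|---|
| 3 | baseline only | 3 |
| 6 | 3, 0 | 3, 6 |
| 12 | 6, 3 | 6, 9 |
| 24 | 12, 6 | 12, 18 |
| 36, 48 or 60 | the two preceding annual visits | 12, 24 |

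The comparison scores can therefore be up to 24 months old. At month 3 the only scheduled earlier evaluation is the baseline itself.

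**3. How large could the effect be?** The documents give no figure for rater bias, so this part rests on an assumption. The inputs from Sample size calculation are a 5-year cumulative incidence of 34% and a planned HR of 1.3. The 34% is reproduced from the stated annual event rate of 8%: 1 − 0.92^5 = 0.341.

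Suppose that true recovery is equal in the two groups and that rating expectation alone moves measured recovery in one group to 34% − d. Under proportional subdistribution hazards, the spurious ratio is ln(1 − 0.34) / ln(1 − (0.34 − d)):

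| d (percentage points) | Calculation | Spurious HR |
|---|---|---|
| 1 | ln 0.66 / ln 0.67 = 0.4155 / 0.4005 | 1.04 |
| 2 | ln 0.66 / ln 0.68 = 0.4155 / 0.3857 | 1.08 |
| 5 | ln 0.66 / ln 0.71 = 0.4155 / 0.3425 | 1.21 |
| 10 | ln 0.66 / ln 0.76 = 0.4155 / 0.2744 | 1.51 |

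(Minus signs cancel.) The table shows sensitivity only. Nothing in the documents selects a row, and a shift in the other direction would shrink or hide a true difference.

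**The case against.** The strongest reply is that the bedside score does not settle the endpoint. A blinded committee rules on recovery, confirmation is composite, the criterion must be met twice and sustained, and assessors are trained and certified to ICC ≥ 0.85. The same-assessor rule applies only when feasible, and rater continuity is a legitimate choice in a study with repeated measurements.

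Much of this stands. A reader might infer that the person who decides recovery always knows the exposure, or that adjudication cannot repair the problem. The documents support neither. The affected person is the bedside rater, the rule is a default, and the safeguards are real. They may still be incomplete. The defining input to adjudication remains the CRS-R score, nothing requires the confirming assessment to have a different rater, and a recovery that the bedside rater never scores may not reach the committee. Certification to an ICC limits disagreement between raters, but it does not blind them.

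Three other inferences go too far:

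- **All three primary outcomes are compromised.** Death is ascertained from civil registration, family notification and hospital records, and cardiovascular events have their own definitions. The argument concerns recovery.
- **A replacement assessor is shown the earlier scores.** The text does not say who makes the comparison or what the new assessor sees. This is a possibility only.
- **Bias of a known size will occur.** The documents support a risk. Choosing the 5-point row and calling it most of the planned effect would present an assumption as a finding.

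**Conclusion.** The point holds as an internal contradiction. The same-assessor rule in Follow-up procedures cannot be reconciled with the blinding statement in Bias control or with the strength claimed in the Discussion, as far as the bedside CRS-R rater is concerned. The consequence is a risk of differential misclassification of recovery by baseline level, partly mitigated by adjudication and composite confirmation.

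Its direction and size cannot be derived from the documents. Under the stated assumptions (equal true recovery, 34% in one group, proportional subdistribution hazards), shifts of 1 to 10 points correspond to a spurious HR of about 1.04 to 1.51. Because the planned HR is only 1.3, the possibility deserves attention. The handover check is a lesser defect: it mixes real change with rater disagreement over gaps of up to 24 months. The correction should be made before enrolment starts in June 2026, because a baseline rating by the later outcome rater cannot be undone.

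**What to change.** Reconcile Follow-up procedures, Bias control and the Discussion in one of two ways.

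1. **Preferred: make the blinding claim true.** Have the follow-up CRS-R that determines emergence from MCS scored by a certified assessor from the existing pool who did not rate that patient's baseline and who has no access in the EDC system to earlier scores. Replace the handover check with two assessors scoring the same session at the time of handover, so that disagreement reflects the raters and not the passage of time.
2. **Minimum: make the claim match the procedure.** If the same-assessor rule is kept, limit the blinding statements in Bias control and the Discussion to the adjudication committee, and record at each visit whether the assessor was blinded to baseline.

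A sensitivity analysis that deletes the unblinded visits is not advised. Those are visits at which recovery is detected, and after month 12 the in-person CRS-R is annual, so removing one visit widens the detection interval from 12 to 24 months.

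The first option needs scheduling rules, EDC access limits and a joint session at each handover. It gives up rater continuity and adds slightly more between-rater noise, which the ICC ≥ 0.85 requirement limits. The documents do not allow the staffing load across 1,000 patients to be costed. The second option costs a change of wording and one data field.
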